### Assessment of secondary outcomes

Secondary outcomes are assessed during index hospitalization and three follow-up telephone interviews at 30 days, and 3 and 12 months following discharge from the index hospitalization. The secondary endpoints include the proportion of patients with a DRA at 3 and 12 months after discharge, duration of DRA, time to first DRA, proportion of patients with a drug-related ED visit, proportion of patients with an all-cause readmission and ED visit, healthcare costs, QoL, cost-effectiveness, number of regular medications, ADL, proportion of patients living independently, proportion of patients with falls and mortality. For all binary outcomes listed above, outcomes are presented as both the proportion of patients experiencing at least one event and the total number of events per patient. In the intervention group, the number and type of recommendations in the pharmacotherapeutic plan and the number of implemented recommendations from the pharmacotherapeutic plan are collected as secondary outcomes.

If an admission or ED visit occurs, more detailed information about the ED visit and medication use is collected from the respective hospital to determine whether the ED visit was drug-related via the AT-HARM10 tool [38]. QoL, ADL and healthcare costs are assessed via the EQ-5D-5L, Katz-6 ADL and iMCQ questionnaires, respectively.

The data concerning medication use at admission and discharge is collected from the EHR during index hospitalization. Medication use during the follow-up period is assessed by asking patients or their representatives about the current medication use during follow-up telephone interviews. The number and types of recommendations in the pharmacotherapeutic plan are determined on the basis of the data collected at baseline about the execution of TMPC. The number of implemented pharmacotherapeutic recommendations is assessed by comparing the recommendations with the medication lists collected during follow-up.

If a patient is unable to answer questions concerning their current medication use during follow-up, the community pharmacy is contacted by the central research team to obtain a medication overview. If a patient cannot be reached, their survival status is identified by calling family members, the GP/elderly care physician or a member of the local research team from the participating hospital.

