**Exclusion criteria**
• No informed consent by patient or a legal representative
• Participation in an interfering clinical trial
• Elective hospital admission
• Direct admission to the intensive care unit
• An estimated life expectancy of less than three months, which includes patients with palliative treatment at home, direct admission to palliative care or palliative care planned within 24 h after index hospital admission
• Patient or legal representative not able to speak Dutch
• Follow-up of patient primarily by healthcare professionals in secondary care. This refers to situations where the secondary caregiver is in the lead of the medication list of the patient instead of the GP or elderly care physician, for example in the following patient groups:
• patients receiving intensive oncological therapy
• patients in an organ- or stem cell transplantation treatment trajectory
• patients receiving intensive (chronic) psychiatric care, such as patients admitted to a medical psychiatric unit
• patients on renal replacement therapy

Patients at the highest risk of a DRA are identified with an externally validated prediction model called the drug-related readmission (DRA) prediction model [23, 25]. The risk percentage for DRA is calculated on the basis of seven characteristics, each accompanied by a regression coefficient (Table 2). The overall DRA risk percentage can be calculated via the following formula: predicted probability = 1/(1 + e^- (−2.41 + characteristic*regression coefficient)) [23]. The 50% of patients at the highest risk of a DRA are selected for this study, resulting in a cut-off percentage of ≥ 23% risk of DRA within 1 year after the index hospitalization according to the prediction model.

**Table 2 Tab2:** Drug-related readmission prediction model, characteristics and regression coefficients. Adopted from Snijders et al. 2023 [23]

Characteristic	Regression coefficient
Number of hospitalizations < 1 year prior to index	
*0*	Ref
*1–2*	0.56
≥*3*	0.94
Non-elective admission	0.24
History of hypertension	0.09
History of chronic kidney disease	−0.05
Use of diuretics	0.47
Use of oral corticosteroids	0.23
Polypharmacy	0.57

If a patient is eligible on the basis of the inclusion and exclusion criteria, the patient (or representative) is informed about the study and informed consent is obtained.

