### Statistical analysis

For patient characteristics, descriptive statistics will be used. The inclusion, exclusion and dropout numbers and reasons will be described. The results will be analyzed via intention-to-treat analysis and per-protocol analysis. The statistical framework for this trial is that of a superiority trial. For the primary endpoint, a generalized linear mixed model with a binomial distribution and logit link function will be used for the analysis at the individual level, adjusting for clustering. In the regression model, the treatment group (intervention/control) and the type of hospital (university/general) are used as a fixed effect and the cluster is used as a random effect. A correction with degrees of freedom is applied (between-within method) in connection with the type I error caused by the small number of clusters.

For DRAs over time (30 days, 3 months and 12 months) an unstructured residual covariance matrix will be included, and the time effect and interaction between time and interventions will be evaluated. A similar model will be applied to other binary outcomes. For these outcomes, the proportion of patients with events and the time to first event will be analyzed, similar to the primary outcome. For the analysis of the continuous secondary endpoints, a linear mixed model with the same random effects and correction method will be used. For all linear outcomes, mean differences with corresponding 95% confidence interval (CI) will be presented, and for binary outcomes, odds ratios with 95% CI will be reported. Mortality over time will be evaluated via multi-level survival analysis, and differences between groups will be presented as hazard ratios with 95% CIs. For ordered variables, multilevel mixed-effects ordered logistic models will be used. Statistical analyses will be performed via STATA 18 (StataCorp. 2023. *Stata Statistical Software: Release 18*. College Station, TX: StataCorp LLC), SPSS (IBM Corp. Released 2023. IBM SPSS Statistics for Windows, Version 29.0.2.0 Armonk, NY: IBM Corp) or RStudio (RStudio Team (2024). RStudio: Integrated Development for R. RStudio, PBC, Boston, MA URL http://www.rstudio.com/).

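### The event rule for binary secondary outcomes does not fit living independently, which is a state with no defined event; fix its definition and take account of living situation at entry

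*Protocol article*

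**What the plan says.** Under Assessment of secondary outcomes, the list of endpoints ends with ADL, "proportion of patients living independently, proportion of patients with falls and mortality". The next sentence covers every binary outcome in that list, without exception: "outcomes are presented as both the proportion of patients experiencing at least one event and the total number of events per patient".

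Under Statistical analysis, the model for DRAs over 30 days, 3 months and 12 months has a time effect and a time-by-intervention interaction. The text then continues: "A similar model will be applied to other binary outcomes". For those outcomes "the proportion of patients with events and the time to first event will be analyzed, similar to the primary outcome". The fixed effects named are treatment group and hospital type, with cluster as a random effect. Mortality gets a separate survival analysis; living independently gets nothing separate.

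Under Data collection, living situation is recorded at baseline, and the current living situation is recorded again at each of the three calls.

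No criterion in Table 1 excludes people who live in a care institution. The secondary-care exclusion applies where "the secondary caregiver is in the lead of the medication list of the patient instead of the GP or elderly care physician", so a patient whose list is led by an elderly care physician remains eligible. The Intervention section explains that this is the nursing home physician.

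**The concern.** Readmissions, ED visits and falls happen at a moment and can recur, so at least one event, number of events and time to first event all make sense for them. Living independently is a condition that a patient is in or not in at each reading. An event rule needs a choice of which state or change counts as the event, and the article makes none.

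What goes wrong depends on that choice:

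- **Event = living independently.** The summary of at least one event asks whether the patient was ever found at home, and the first call nearly settles that. A later move into care does not change it.
- **Event = loss of independent living.** Later moves are counted. Patients in care at entry, however, have no time at risk for a first loss, and they enter the proportion as a constant unrelated to the intervention.

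At stake is the clarity and sensitivity of one secondary endpoint. This is more than detail left to an analysis plan, because the article states a rule and the rule does not suit the variable.

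**Working it through.** **1. The article's own figure.** Nothing is stated for living independently, so the sample size serves only to confirm the cluster inputs. For 20% vs 14%, two-sided 5%, power 80%, the two-proportion formula gives 615 per arm. Design effect = 1 + (153 − 1) × 0.0065 = 1.988. 615 × 1.988 = 1,223, against 1,224 stated. It reproduces.

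**2. What each event definition shows.** Every rate here is an assumption; the article gives none. Let 10% be in care at entry. Among the rest, let cumulative moves into care by 30 days, 3 months and 12 months be 3%, 6% and 15% (control) and 3%, 4.5% and 9% (intervention), with no deaths or returns home.

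| Summary | Control | Intervention | Difference |
|---|---|---|---|
| Independent at one or more calls, all patients | 0.90 × 0.97 = 87.3% | 0.90 × 0.97 = 87.3% | 0 |
| Number of calls at which independent, mean | 0.90 × (0.97 + 0.94 + 0.85) = 2.48 | 0.90 × (0.97 + 0.955 + 0.91) = 2.55 | +0.07 |
| State at 12 months, all patients | 0.90 × 0.85 = 76.5% | 0.90 × 0.91 = 81.9% | +5.4 points |
| Not independent at one or more calls, all patients | 10 + 0.90 × 15 = 23.5% | 10 + 0.90 × 9 = 18.1% | −5.4 points |
| Loss among those independent at entry | 15% | 9% | −6 points |

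The first row misses the whole difference. The fourth row sees it, but 10 of its 23.5 and 18.1 points were fixed before the intervention began. With 5% to 20% in care at entry, and 12-month moves of 15% vs 9% or 25% vs 15%, the first row stays at 0 while the 12-month state differs by 4.8 to 9.5 points.

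**3. Gain from taking account of living situation at entry.** Assumptions: share b in care at entry and staying there; loss by 12 months of 15% vs 11% among the rest; ICC 0.0065, which the article gives for DRAs and which is borrowed here.

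Power = Φ(|difference| / SE − 1.96), with SE = √{[p₁(1 − p₁) + p₂(1 − p₂)] × DE / n}.

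- *All patients, unadjusted:* n = 1,224 per arm, DE = 1.988, proportions independent (1 − b) × 0.85 and (1 − b) × 0.89. At b = 10%: 76.5% vs 80.1%, SE = √(0.3392 × 1.988 / 1,224) = 0.0235, 0.036 / 0.0235 = 1.53, power about 33%.
- *Independent at entry only:* n = 1,224 × (1 − b), cluster size 153 × (1 − b). At b = 10%: n = 1,101.6, DE = 1 + 136.7 × 0.0065 = 1.889, SE = √(0.2254 × 1.889 / 1,101.6) = 0.0197, 0.04 / 0.0197 = 2.03, power about 53%.

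| In care at entry | All patients | At risk only |
|---|---|---|
| 5% | 42% | 54% |
| 10% | 33% | 53% |
| 15% | 27% | 52% |
| 20% | 23% | 50% |

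At the article's upper ICC of 0.01, the ranges are 35-19% and 45-42%. The planned between-within degrees of freedom (about 13 with 16 clusters, critical value 2.16) would lower all of these, so the comparison between columns is what counts.

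**The case against.** The best defence is that the rule is loose drafting aimed at recurrent events. The same list contains mortality, for which a number of events per patient is meaningless, and mortality has its own survival analysis. The endpoint is named as a proportion, the state is collected at every call, and the model for other binary outcomes follows directly on one with time and time-by-intervention terms. On that reading, the state at each time point is already analysed. Much of this stands, and it limits the point. It does not settle it: mortality is redirected elsewhere in the text and living independently is not, and the number of events and time to first event still have no defined meaning for it.

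Stronger readings might be inferred but are not supported:

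- *Both harms occur together.* They come from opposite event definitions, and the article adopts neither.
- *Later moves into care are hidden.* Only the summary of at least one event, on one definition, misses them. The model over time can show them, and even the count of calls picks up part.
- *Care-home residents cannot be scored.* They can be, on the state at each call. Only a first loss, and the time to it, is undefined for them.
- *The all-patient analysis will be biased by imbalance at entry.* If 5% vs 10% were in care at entry, with 12% loss in both arms and no effect, the result would be 95% × 0.88 = 83.6% vs 90% × 0.88 = 79.2%, an odds ratio of 1.34. With design effect 1.988, z is about 1.99, below the critical value of 2.16 on about 13 degrees of freedom; at ICC 0.01 it is about 1.77. On the formula √{2p(1 − p) × DE / 1,224}, with p of 5-10%, the chance SD of the arm difference at entry is 1.2 to 1.7 points. A gap of 5 points is thus 3 to 4 SDs and would need strong differential recruitment. Screening is described as consecutive, and no figure in the article suggests such selection.

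That all patients form the denominator is likewise inferred, from the intention-to-treat statement and the absence of a named subset.

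**Conclusion.** The point holds in a limited form. As written, the event rule covers living independently, the event is undefined, and either possible definition gives a poor summary. The model over time could still report the state properly, but living situation at entry, although collected, is not among its stated terms.

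The size cannot be fixed from the article, because the share in care at entry and the rates of loss are not given. Under the assumptions in the working, taking account of living situation at entry raises power from about 42-23% to about 54-50%. That gain comes from conditioning on the state at entry, not from dropping the event rule alone. This is a minor point on one secondary endpoint; the primary analysis, the sample size and the data collection are untouched.

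**What to change.** State that living independently is exempt from the number-of-events and time-to-first-event rule, and define what is counted. Then choose one of these:

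1. Analyse the state at 30 days, 3 months and 12 months with the planned binary mixed model, adjusted for living situation at entry.
2. Analyse loss of independent living at those times among patients who lived independently before the index admission, with the all-patient proportion given descriptively.

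Either way, say how patients who die before a call are handled; in a high-risk population aged 70 and over this cannot be left implicit. If hardly any resident moves back home, the covariate in option 1 nearly determines the outcome for residents and the model may be unstable; option 2 is then the practical choice.

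The cost is a change of wording, since living situation is already collected at baseline and at every call. The drawback of option 2 is that residents at entry leave the denominator of this endpoint.

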### Data management

Patient data are collected from the EHR and questionnaires; responses are directly entered into a Castor® Electronic Data Capture (EDC) database, version 2024.1.0.3. (Castor, Amsterdam, The Netherlands) [39], hosted by Radboudumc, in which the participant data are automatically pseudonymized using a patient- and hospital-specific number. Data entry is monitored throughout the study period via built-in error notifications in the Castor® database. During the study period, data can only be made available for the study group upon request by a methodologist. The final trial dataset will be available for all data managers involved in the study (from the Radboudumc, Amsterdam UMC and the methodologist of Trialbureau Zorgevaluatie Nederland). After the final data cleaning, the dataset will be made available for analysis to the study group. After the trial is completed, the data will be anonymously published in a repository and made available upon reasonable request. More elaborate information about data management can be found in the study’s data management plan (available upon request).

### Sample size calculation

For the calculation of the sample size, we estimated that the proportion of patients with a DRA in the target group studied is approximately 20% [5]. Previous studies have indicated that multicomponent interventions with a focus on medication optimization can achieve a decrease in DRAs of 6%, i.e., a total readmission rate of 14% [20, 40, 41]. Using a sample size of 1,224 patients in both the intervention and control groups, which are divided into eight clusters of 153 patients in each group, a 6% decrease can be detected from the standard readmission rate of 20% (two-sided, power 80%, alpha 5%). An intracluster correlation coefficient (ICC) of 0.0065 was used, which is based on an estimated ICC between 0.005 and 0.01. With an ICC of 0.01, this group size would be sufficient to demonstrate a one-sided difference of 6% in favour of the intervention. A drop-out rate of 5% is expected [42], requiring a total of 161 patients per cluster to be included, or 2,576 in total. The sample size was calculated via PASS 2020 Power Analysis and Sample Size Software (NCSS, LLC. Kaysville, Utah, USA).

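### The stated 80% power holds only with normal critical values; under the planned two-sided test with 16 hospitals it is about 74%, and about 64% at the upper ICC of 0.01

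*Protocol article*

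**What the plan says.** All of the power statements are in the protocol article under Sample size calculation.

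- Control rate: "we estimated that the proportion of patients with a DRA in the target group studied is approximately 20"%.
- Effect: the intervention "can achieve a decrease in DRAs of 6%, i.e., a total readmission rate of 14"%.
- Size: "Using a sample size of 1,224 patients in both the intervention and control groups". Each arm has eight hospitals with 153 patients apiece.
- Claim: "a 6% decrease can be detected from the standard readmission rate of 20% (two-sided, power 80%, alpha 5"%).
- ICC: "An intracluster correlation coefficient (ICC) of 0.0065 was used, which is based on an estimated ICC between 0.005 and 0.01".
- Upper ICC: "With an ICC of 0.01, this group size would be sufficient to demonstrate a one-sided difference of 6% in favour of the intervention".

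Under Statistical analysis, the primary endpoint is analysed with a logistic mixed model. Treatment and hospital type are fixed effects and hospital is a random effect. "A correction with degrees of freedom is applied (between-within method"), and the reason given is the type I error that arises with a small number of clusters. Results are to be reported as odds ratios with 95% confidence intervals. No one-sided test is planned. The sample size section mentions no small-sample correction.

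**The concern.** The two sections describe different tests. The analysis section accepts that normal critical values are too lenient with 16 hospitals and corrects for it. The sample size section appears to have used those same normal values. Treatment varies only between hospitals, so the correction applies directly to the treatment effect and costs power that the plan has not counted.

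The sentence about ICC 0.01 adds to this. It reassures the reader that the upper end of the ICC range is covered, but only by moving to a one-sided comparison, whereas the main claim and the analysis are two-sided.

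At stake is how a null result is read. A reader told that the trial had 80% power will take a non-significant result as fairly strong evidence against a 6-point reduction. The Discussion also says that between-hospital variability was allowed for in the power analysis. If the true power is 64 to 74%, between about a quarter and a third or more of true 6-point effects would be missed.

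**Working it through.** **Inputs.** From Sample size calculation: p₁ = 0.20, p₂ = 0.14, m = 153 per hospital, 8 hospitals per arm (1,224 per arm), ICC 0.0065 within a range of 0.005 to 0.01, alpha 5% two-sided. From Study design and setting: 16 hospitals. From Statistical analysis: fixed effects for treatment and hospital type, between-within degrees of freedom.

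**Formulas.** Design effect DE = 1 + (m − 1) × ICC. Effective size per arm nₑ = 1,224 / DE. Unpooled variance term = 0.20 × 0.80 + 0.14 × 0.86 = 0.2804 (pooled: 2 × 0.17 × 0.83 = 0.2822). Noncentrality λ = 0.06 / √(variance term / nₑ).

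**Step 1: reproduce the stated figure (ICC 0.0065).**
- DE = 1 + 152 × 0.0065 = 1.988; nₑ = 1,224 / 1.988 = 615.7.
- λ = 0.06 / √(0.2804 / 615.7) = 2.81 (2.80 pooled).
- Normal-based two-sided power = Φ(λ − 1.96) = 80.3% (80.0% pooled).
- In reverse, a two-proportion comparison needs 615 per arm without clustering; 615 × 1.988 = 1,223, against 1,224 stated.

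The stated 80% is therefore a normal-based result.

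**Step 2: reproduce the ICC 0.01 sentence.**
- DE = 1 + 152 × 0.01 = 2.52; nₑ = 485.7; λ = 2.50 (2.49 pooled).
- Normal-based one-sided 5% power = Φ(λ − 1.645) = 80.3% (80.1% pooled).
- Normal-based two-sided 5% power = 70.4% (70.2% pooled).

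The sentence works as a one-sided 5% normal test at 80% power. The article prints neither alpha nor power in that sentence, so both are inferred.

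**Step 3: apply the planned test.** Between-hospital degrees of freedom = 16 hospitals − 3 (intercept, treatment, hospital type) = 13. The two-sided 5% critical value is 2.16. Power comes from the noncentral t distribution with noncentrality λ. Ranges cover pooled and unpooled variance.

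| ICC | DE | Normal, two-sided | t with 13 df, two-sided |
|---|---|---|---|
| 0.005 | 1.760 | 85% | 78.6–78.9% |
| 0.0065 | 1.988 | 80.0–80.3% | 73.6–73.9% |
| 0.0075 (midpoint of range) | 2.140 | 77% | 70.5–70.7% |
| 0.01 | 2.520 | 70.2–70.4% | 63.4–63.7% |

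With 14 df (hospital type not counted) the figures are 79.1–79.3%, 74.1–74.4% and 63.9–64.2% at ICC 0.005, 0.0065 and 0.01. On the log-odds scale with 13 df they are 73.2% at ICC 0.0065 and 63.0% at 0.01. The one-sided 5% test at ICC 0.01 also falls short once 13 df are used: 76.2–76.4%.

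**Step 4: simulation check.** Beta-binomial hospital data, analysed on hospital proportions with adjustment for hospital type (13 df, 40,000 replicates), gave 73.3% at ICC 0.0065 and 63.5% at 0.01. In a separate 6,000-run simulation under no effect, the normal critical value rejected in 7.3% of runs and the 13-df value in 4.9%. The correction is needed.

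**Step 5: detectable difference at ICC 0.0065, 13 df.** A 6.4-point difference from 20% has 79.3–79.6% power and a 6.5-point difference has 80.6–80.9%. The 80% point is therefore between 6.4 and 6.5 points, not 6.0.

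**Step 6: unequal hospitals (assumption only).** The article gives no spread of cluster sizes. With DE = 1 + ((1 + CV²) × 153 − 1) × ICC and 13 df, power at ICC 0.0065 and 0.01 is 73% and 63% for a CV of 0.2, 71% and 60% for 0.4, and 67% and 55% for 0.6. The main result does not depend on these values.

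**The case against.** - **No arithmetic slip.** The stated numbers reproduce, and the use of normal critical values is inferred because the software settings are not shown. This is correct: the problem is a mismatch between the planning test and the analysis test. The inference is strong, though. A normal calculation reproduces both sentences almost exactly, while a t-based one misses 80% by about 6 points.

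- **The ICC 0.01 sentence is openly labelled one-sided and prints no power.** That is also true, so it is not a false statement in itself. But no one-sided test is planned, so it says nothing about the power of the trial as it will be analysed.

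- **0.0065 lies within the stated range, and no midpoint was claimed.** This stands. The choice is not an error. It happens to be where normal-based power meets 80%, and no inference about intent is warranted. The fair presentation is the whole range, about 64 to 79%.

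- **Adjusting for hospital type may remove some between-hospital variance.** This is the best statistical point. If type explained 10%, 20% or 30% of that variance (an assumption), power at ICC 0.0065 with 13 df would be 76%, 78% or 80%. The article does not say whether 0.0065 is before or after adjustment, and it claims no such gain. At ICC 0.01 even a 30% reduction gives only 72%.

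- **Inclusion is closed, and the analysis remains valid.** Both are true. The degrees-of-freedom correction protects the type I error, and nothing about conduct changes. The stated power will nevertheless be used to interpret the result.

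**Conclusion.** The concern holds. For the two-sided 5% test that the protocol plans, power to detect 20% versus 14% is about 74% at the chosen ICC of 0.0065, not 80%. At ICC 0.01 it is about 64%; of the 16-point gap from the 80% implied there, about 10 points come from replacing the one-sided test with a two-sided one and about 6 from the degrees of freedom. At the most favourable ICC in the stated range, 0.005, power is about 79%, so 80% is not reached anywhere in that range.

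The result rests on the protocol's own rates, equal clusters of 153 after dropout, 13 or 14 between-hospital degrees of freedom, and an ICC not reduced by adjustment for hospital type. Unequal recruitment would lower the figures; a strong hospital-type effect would raise them. The validity of the primary analysis is not affected.

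**What to change.** In Sample size calculation:

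1. State that the 80% was obtained without the small-sample correction, and give two-sided power for the planned test (t with 13 df): about 79%, 74% and 64% at ICC 0.005, 0.0065 and 0.01. Base these on the hospital sizes actually recruited, since inclusion has ended, and say whether the ICC is before or after adjustment for hospital type.
2. Alternatively, keep 80% power and give the detectable difference at ICC 0.0065 as about 6.5 points.
3. Replace the one-sided sentence with the two-sided figure at ICC 0.01.

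The cost is wording only: no added patients or hospitals and no change to the analysis. The price is a less favourable stated power. Reaching 80% by size alone at ICC 0.0065 would have needed about 213 analysed patients per hospital (213 × 16 = 3,408, against 153 × 16 = 2,448). That is not proposed here.
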